#### Sample size

There is a paucity of guidance for sample size justification for field test methods. With the primary objectives being feasibility of use in the clinical setting, we will aim to recruit a sample of 30 patient participants. This sample size is consistent with minimum numbers required to demonstrate adequate feasibility in pilot studies [56], and consistent with other pre-/post-studies testing PtDAs with patients facing the decision [57–59]. Based on usual referral volumes, we expect to recruit 3 patients per month and complete study recruitment after 10–12 months.

#### Data management and analysis

Quantitative data will be uploaded and stored in an encrypted Microsoft Excel spreadsheet. As the focus of the field test is on feasibility rather than efficacy outcomes, analysis will be primarily descriptive with baseline participant characteristics and feasibility data presented using frequencies and percentages. Tests for data normality will be performed and summarized using means and standard deviation if normally distributed, and medians and ranges if not. For post-test only outcomes (acceptability, PDMS), patients’ responses will be summarized and described. For pre-/post-test outcomes (knowledge and SURE test), questionnaires will be compared using the student t-test if normally distributed and using the Wilcoxon rank-sum test if not. Data will be disaggregated by sex and gender to examine how these variables may affect patient and clinician experience with the PtDA and associated outcome measures. Qualitative data from the semi-structured interviews will be transcribed verbatim and analyzed using thematic analysis as described for alpha testing.

There are no known defined standards for determining success of field testing measures. As such, we have determined the following a-priori criteria as determinants for success of the field test: (1) no insurmountable barriers identified from semi-structured interviews or open-ended feedback based on review from the steering group, (2) minimum of 80% targets for feasibility outcomes, (3) minimum of 66% of participants find the PtDA acceptable and balanced, (4) minimum score of 66 on the PDMS (5) 66% demonstrate nominal improvement on pre-/post-test outcomes for desired impact (knowledge and SURE). For the SURE test, an overall finding of > 66% participants responding with a 4/4 score will also be deemed a measure of success. If the cutoffs for determining success of the field test are not reached, revisions to the PtDA will be discussed and implemented by the steering group with further recruitment and testing at the discretion of the steering group.

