**Methods:**

This is a three-stage study protocol. First, we will assemble a multi-disciplinary steering group including patients, clinicians, educators, and researchers to develop the patient decision aid prototype using the Ottawa Decision Support Framework. Second, we will perform a mixed-methods alpha test of the decision aid prototype with patients and clinicians experienced in acute Achilles tendon ruptures. Outcomes measured will include acceptability and usability of the patient decision aid measured using validated outcome scales and semi-structured interviews. A minimum of three rounds of feedback will be obtained. Results will be analyzed using descriptive statistics, reviewed by the steering group, to guide revisions to decision aid prototype at each round. The third stage will be field testing the revised decision aid prototype in usual clinical care. A pre-/post-study will be performed with patients with acute Achilles tendon ruptures. Patients will be recruited from the emergency department and complete the pre-consultation decision aid prior to a one-week follow up with their surgeon. The primary outcome of field testing will be feasibility of implementing the decision aid in the clinical setting and will be measured with recruitment and completion metrics. Secondary outcomes include acceptability of the decision aid, knowledge, preparedness for decision making, and decisional conflict, measured using validated outcome measures. Statistical analysis will be performed using descriptive analysis for primary outcomes and a student t-test and Wilcoxon Rank-Sum test for secondary outcomes.

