### Stage 3: field testing the revised PtDA prototype

Field testing by end users is a critical component of PtDA development as identified by IPDAS [19]. As opposed to the alpha testing, field testing solicits feedback on the PtDA from patients within the typical clinical setting. The primary outcome of the field testing is to evaluate the feasibility of using the PtDA at the point-of-care and to guide any final revisions, with secondary outcomes including acceptability, and potential of the PtDA to have the desired impact without adverse consequence.

We will perform a field test of the revised paper-based, pre-consultation PtDA prototype resulting from the alpha testing phase using a pre-/post-test study design and embedded qualitative feedback. A pre/post-test design has been chosen as it allows for evaluation of the secondary outcomes of the PtDA having the desired impact, which will provide us with baseline data to calculate a sample size for a larger evaluation study [47]. The prototype will be given to patients following initial presentation with the injury in the emergency department and self-administered by the patient at home prior to final treatment consultation with the orthopaedic surgeon.

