#### Procedure

The procedure flow for patient recruitment is summarized in Fig. 3. Upon consultation from the emergency department physician, a member of the orthopaedic team (resident, staff physician or physician assistant) will meet patients presenting with an acute Achilles tendon rupture. The orthopaedic team will confirm the diagnosis, discuss the diagnosis and management options with the patient. Concurrently, they will verify if the patient meets inclusion criteria, discuss the study procedures, answer patients’ questions, and obtain the patients’ signed consent to participate. The patient will be asked to complete a baseline questionnaire including questions about their demographics (age, sex, gender, occupation, highest level of education) and secondary outcome measures. The patient will be splinted in plantarflexion in keeping with standard practice and given a copy of the PtDA to review and complete in preparation for their follow-up appointment in the orthopaedic clinic.

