**Fig. 3 Fig3:**
[figure not shown]
Patient participant study procedure

As per usual clinical practice, patients will be given a follow-up appointment in the orthopaedic plaster room 3–5 days following their emergency department visit. At the plaster room, the orthopaedic resident or surgeon will discuss the treatment options, answer patients’ questions and make the treatment decision with the patient. Either immediately following or within 2 weeks, the research assistant will ask the patient to complete a questionnaire including the secondary outcome measures and conduct the semi-structured interview.

We will also obtain feedback from orthopaedic residents and surgeons who consulted with patients in the study to determine the clinician experience with patients using the PtDA. After the last patient is recruited, these orthopaedic surgeons will be sent a link to an online survey using the SurveyMonkey (San Mateo CA) platform to elicit feedback on the PtDA.

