Acceptability of the PtDA, will be evaluated using the OAT[49] previously used in the alpha test phase. This validated instrument measures key outcomes including; amount of information, length, clarity and balanced presentation, which is important for avoiding biased presentation of information on options.

To evaluate whether the PtDA potential to have the desired impact without adverse consequence, patients will complete a knowledge test[50] and the SURE test[31] as a pre-/post-outcome and the Preparation for Decision Making Scale (PDMS) [51] as a Post-PtDA outcome measure.

Patient knowledge will be measured using a knowledge test developed by the steering group and embedded within the PtDA. The test will be adapted from the template available on the Ottawa Decision Support Group website [50] and will consist of 4–6 questions about key content important to know when making this decision. This format has been adapted for several clinical conditions and been shown to have high internal consistency and validity. Patient knowledge of their specific pathology and treatment options underlies one of the pillars of informed consent [52], and improved decision quality is based on patients making an informed, value-based decision [13].

The SURE test will be used to screen patients for decisional conflict [31]. It has four questions with ‘yes’ or ‘no’ responses in the domains of certainty, knowledge, values and support. Any ‘no’ answer is indicative of clinically significant decisional conflict. This test has been validated in a range of clinical settings [53, 54].

We will use the Preparation for Decision Making Scale (PDMS) [51] to measure patients’ perceived usefulness of a PtDA in preparing for a medical consultation. This specifically measures the IPDAS criteria for the quality of the decision process. This instrument consists of 10 questions to be ranked on a 5-point Likert scale, has both high reliability and internal consistency with a Cronbach’s alpha of 0.92–0.96 [55].

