### Strengths and limitations

A major strength of this protocol lies in the use of an iKT approach to develop the PtDA. This approach has been demonstrated to maximize knowledge users input, increase use, and improve impact [22]. We have adhered to a rigorous methodology guided by the ODSF and the IPDAS to ensure the PtDA is developed to a high quality standard [60]. Additionally, engaging stakeholders from multiple disciplines and Canadian locations in the development and alpha testing of the PtDA will ensure the end product is usable and optimized to meet the needs of a variety of patients and clinicians. This approach will also raise early awareness of the PtDA’s existence, necessary for achieving our of aim of public availability and national dissemination. Additionally, the inclusion of qualitative methods allows for collection of deeper stakeholder insights, perceptions and opinions [61], all of which are critical in designing a PtDA that will optimize user uptake.

Limitations of this study protocol include the arbitrary success endpoints for both alpha and field testing outcomes. To our knowledge, discrete success endpoints have not been previously described. Our endpoints remain largely qualitative and at the discretion of the steering committee. Despite this, we are using methods recommended by IPDAS [19], and will have steering committee members with expertise in PtDA development and evaluation. Further work and study to better define these endpoints is necessary. Additionally, the sample is unlikely to allow us to identify sex and gender-specific differences from either patients or clinicians because it will likely be majority male, reflecting the populations represented; Achilles tendon ruptures occur far more frequently in men [2], and orthopaedic surgeons are disproportionately male. Nonetheless, our analysis plan details an effort to capture and analyze these differences. Finally, there are inherent limitations of the before/after study design, including the lack of a control arm. This makes it difficult to control for confounding factors that may affect patient outcomes, such as independent research into treatment options. However, the design been previously used in the evaluating PtDAs [47] and offers the advantage of facilitating patient recruitment.

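### The pre/post knowledge and SURE scores come from the same patients, but the plan names the Wilcoxon rank-sum test, an independent-samples test, and a Student t-test not stated to be paired

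*Protocol article*

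**What the plan says.** The field test is run "using a pre-/post-test study design and embedded qualitative feedback" (Stage 3, opening section). Under Stage 3, Outcomes and instruments, "patients will complete a knowledge test[50] and the SURE test[31] as a pre-/post-outcome". The two measurements come from the same people:

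- **Before.** In the emergency department, "The patient will be asked to complete a baseline questionnaire including questions about their demographics". The Procedure section adds that this questionnaire also contains the secondary outcome measures.
- **After.** Following the plaster room visit, immediately or within two weeks, "the research assistant will ask the patient to complete a questionnaire including the secondary outcome measures".

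There is no second group. Strengths and limitations concedes that "there are inherent limitations of the before/after study design, including the lack of a control arm".

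For these two outcomes, Data management and analysis states that "questionnaires will be compared using the student t-test if normally distributed and using the Wilcoxon rank-sum test if not". The Methods part of the abstract repeats it as "a student t-test and Wilcoxon Rank-Sum test for secondary outcomes". The terms paired and signed-rank appear nowhere in the article.

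**The concern.** The Wilcoxon rank-sum test compares two independent samples. Here the two columns of scores are two readings on one set of patients, so the test treats 30 linked pairs as 60 unrelated observations. It ignores the pre/post correlation, and its null distribution is then wrong.

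The rank-sum branch is also the likelier one. SURE has four yes/no items and the knowledge test has four to six questions. Scores this coarse, from about 30 patients, will probably not pass a normality test. That is a prediction, not something the document states.

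With positive correlation, a real gain in knowledge or fall in decisional conflict could be reported as non-significant. The Stage 3 introduction says the pre/post data will also be used to size a larger evaluation study, so it matters that within-patient change is analysed and reported as such.

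**Working it through.** **The plan's own figure.** The sample size of 30 rests on precedent from pilot and pre/post studies, not on a power formula. There is therefore no stated power to reproduce. The recruitment arithmetic fits: 30 / 3 per month = 10 months.

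**Inputs**
- From the article: n = 30 patients, one group, two readings each; SURE scored 0–4; knowledge test of 4–6 items.
- Assumed, because the article gives none: two-sided alpha 0.05, no dropout, a shift of d = 0.5 SD (0.8 SD as a check), and pre/post correlation r from 0 to 0.7.

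**Formulas** (normal approximation, SD = 1 at both times)
- Standard error used by an unpaired test: SE_u = sqrt(2/n) = sqrt(2/30) = 0.258.
- True standard error of the mean change: SE_p = sqrt(2(1 − r)/n).
- Ratio: SE_u / SE_p = 1/sqrt(1 − r).
- Actual type I error of the unpaired test: 2[1 − Φ(1.96 × SE_u/SE_p)].
- Power, unpaired: Φ((d − 1.96 × SE_u)/SE_p). Power, paired: Φ(d/SE_p − 1.96).

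**Worked case, r = 0.5, d = 0.5.** SE_p = sqrt(1/30) = 0.183 and the ratio is 1.41.
- Unpaired power: Φ((0.5 − 0.506)/0.183) = Φ(−0.03) = 49%.
- Paired power: Φ(2.74 − 1.96) = Φ(0.78) = 78%.
- Type I error: 2[1 − Φ(2.77)] = 0.006.

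| r | SE ratio | Type I error, unpaired | Power, unpaired | Power, paired |
|---|---|---|---|---|
| 0 | 1.00 | 0.050 | 49% | 49% |
| 0.3 | 1.20 | 0.019 | 49% | 64% |
| 0.5 | 1.41 | 0.006 | 49% | 78% |
| 0.7 | 1.83 | 0.0003 | 48% | 94% |

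**Rank tests by simulation, normal scores.** With 30 pairs and a 0.5 SD shift, rank-sum power is about 43–46% for r = 0.3 to 0.7. Signed-rank power is about 60%, 74% and 92% at r = 0.3, 0.5 and 0.7.

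**Rank tests by simulation, scores on a 0–4 scale** (4,000 runs per setting, 0.5 SD shift on the underlying scale)

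| r | Type I error, rank-sum | Power, rank-sum | Power, signed-rank |
|---|---|---|---|
| 0 | 0.049 | 44% | 42% |
| 0.3 | 0.018 | 43% | 53% |
| 0.5 | 0.009 | 40% | 65% |
| 0.7 | 0.002 | 38% | 82% |

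On a 0–5 scale the pattern is the same, with a rank-sum type I error of 0.024 at r = 0.3.

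**Sensitivity to the shift.** At d = 0.8 and r = 0.5, unpaired power is Φ((0.8 − 0.506)/0.183) = Φ(1.61) = 95% and paired power is Φ(4.38 − 1.96) = Φ(2.42) = 99%. By simulation, rank-sum gives about 91% and signed-rank about 98%. The loss is then small.

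**Sensitivity to sign.** At r = −0.3 the SE ratio is 0.877 and the type I error is 2[1 − Φ(1.72)] = 0.086, so the test would reject too often. Repeated scores are usually positively correlated, so this is the less likely direction.

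**The case against.** The best case on the other side is that little depends on these tests. Feasibility is the primary outcome, the analysis is described as mainly descriptive, and n = 30 was not chosen for power. The 80% and 66% success criteria use no p-value, and the knowledge and SURE criterion already counts patients who improve, which is a within-patient measure. With positive correlation the error is conservative and would not produce a false claim of benefit. All of this stands. It limits the weight of the point but does not make the rank-sum test right.

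Some stronger readings are tempting, and the document does not support them:
- **That the t-test is also wrong.** Student t-test covers the paired form too. The article omits the word; it does not state the wrong version. Naming it beside rank-sum suggests the unpaired form but does not settle it.
- **That confidence intervals will be wrong.** No interval is planned for these outcomes.
- **That the inputs for the larger study are lost.** Counting improvers requires scores linked by patient, so the SD of change and the correlation stay computable whichever test is run. They are just not among the planned outputs.
- **That SURE should have been analysed as paired binary data.** The article notes that any negative reply "answer is indicative of clinically significant decisional conflict", but its 4/4 criterion applies to the post-test only. A McNemar test would be an addition, not a correction.
- **That a normality check is itself an error.** Dropping it is a matter of preference.

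**Conclusion.** The named non-parametric test is wrong as written, in both the analysis section and the abstract, and the t-test needs the word paired. Any p-value from an independent-samples test on these data is invalid unless the pre/post correlation is exactly zero.

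The size depends on a correlation and a shift that the document does not give. Over the assumed r = 0.3 to 0.7, a moderate shift costs roughly 15 to 45 percentage points of power on normal scores and 10 to 44 points on a 0–4 score (43% against 53%, up to 38% against 82%). There is no cost at r = 0, and at 0.8 SD with r = 0.5 it is only a few points.

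This is an error of moderate weight. It affects the only hypothesis tests named for the field test, but these concern secondary outcomes, and no success criterion or decision to revise the aid depends on them.

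**What to change.** In Data management and analysis and in the abstract's Methods:
- replace *Wilcoxon rank-sum test* with *Wilcoxon signed-rank test*;
- replace *student t-test* with *paired t-test*;
- in the analysis section, say that normality is judged on the within-patient differences.

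Add that the SD of change and the pre/post correlation will be reported for knowledge and SURE, since the data are meant to help size a larger study.

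An exact McNemar test of SURE 4/4 against less than 4/4 is optional.

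The cost is a sentence or two of wording in each place. No extra patients, visits or data are needed, because the scores must already be linked by patient to count those who improve.

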#### Outcomes and instruments

Field test outcomes of interest have been chosen based on those recommended by IPDAS [18]. Field test outcomes are summarized in Table 1 and include: (1) feasibility of PtDA administration and use by patients, (2) barriers to PtDA use among patients and clinicians, (3) patients’ acceptability of the PtDA, and (4) potential of the PtDA to have the desired impact without adverse consequence.

**Table 1 Tab1:** Summary of field test outcome measures

Outcome	Instruments	Measure of Success
1. Feasibility		
a. Patients		
	Metrics of use	At least 80% recruitment
		At least 80% PtDA completion
		At least 80% data completion
b. Surgeons	Patient semi-structured interview	Identifying resolvable barriers to PtDA use
	Metrics of use	At least 80% use for eligible patients
	Surgeon survey	Identifying resolvable barriers to PtDA use
2. Acceptability		
Amount of information	Post-PtDA	At least 66% perceive as acceptable
Length	Patient acceptability questionnaire	
Clarity		
Balance of presentation		
3. Potential for PtDA to have desired effect without adverse consequence		
	Post-PtDA	
	Patient preparation for decision making scale (PDMS)	Score of at least 66/100
	Practitioner preparation for decision making scale (PDMS)	Score of at least 66/100
	Pre- and post-PtDA	
	Knowledge test	At least 66% demonstrate improvement from pre to post PtDA administration
	SURE test	66% demonstrate improvement from pre to post PtDA administration
		And/or:
		> 66% Score 4/4 on post PtDA SURE test

Specific patient feasibility metrics will include the (1) percent of screened eligible patients recruited, (2) reasons for ineligibility, (3) percentage of recruited patients that completed the PtDA prior to the follow-up appointment and the (4) percentage of missing data on follow up outcome questionnaires. We will set a level of success at 80% participant recruitment of those meeting eligibility, 80% participant completion of the PtDA, and 80% minimal completed data on follow up questionnaires, in keeping with levels set in previously performed field tests [48].

The semi-structured interview with the patients will ask them to share their experiences on using the PtDA, their experiences discussing the decision with the orthopaedic surgeon, suggestions to improve the process of using the PtDA, formatting, and any barriers to use.

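### The 66% improvement rules count patients already at the maximum as failures, and the stand-alone SURE rule ignores baseline and worsening

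*Protocol article*

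**What the plan says.** In the Protocol article, Stage 3, Data management and analysis, the fifth a-priori success criterion is that "66% demonstrate nominal improvement on pre-/post-test outcomes for desired impact (knowledge and SURE"). Table 1 (Outcomes and instruments) gives the knowledge rule as "At least 66% demonstrate improvement from pre to post PtDA administration" and states no alternative to it. For SURE, Table 1 joins the improvement rule by and/or to a second one, that more than "66% Score 4/4 on post PtDA SURE test". The analysis section confirms that the second rule is enough for SURE on its own: "For the SURE test, an overall finding of > 66% participants responding with a 4/4 score will also be deemed a measure of success".

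Table 1 places these rules under the outcome "Potential for PtDA to have desired effect without adverse consequence". SURE has four yes/no items and the knowledge test will have four to six questions (Outcomes and instruments). Under Sample size, "we will aim to recruit a sample of 30 patient participants". Nowhere does the article limit the improvement percentage to patients who have room to improve, or credit a patient who stays at the maximum.

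**The concern.** There are two separate weaknesses in rules that the article fixes in advance.

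- **Ceiling.** A patient with full marks before the aid can only stay or fall. The improvement rule treats staying as failure, so a working aid can miss the knowledge criterion because patients began well informed. The article itself makes some ceiling plausible. At the emergency visit the orthopaedic team will "discuss the diagnosis and management options with the patient", and the text describes this before the baseline questionnaire at the same visit (Stage 3, Procedure).
- **No baseline term and no count of worsening.** The 4/4 route for SURE looks only at the score after the aid. If most patients were already at 4/4, it passes with no change, or even with a net fall. The outcome's label promises absence of adverse consequence, but neither pre/post rule counts a patient who moves from 4/4 to a lower score, which the article regards as clinically significant decisional conflict.

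At stake is a wrong reading of one success criterion. That could prompt needless revision and further recruitment at about three patients a month, or give false reassurance about decisional conflict.

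**Working it through.** **Inputs.** n = 30 (Sample size). Cutoff 66% improved, read as at least 66%, and more than 66% at 4/4 for the SURE alternative (Table 1; Data management and analysis). The sample size is justified by precedent and feasibility, so there is no power calculation to reproduce. Its one piece of arithmetic holds: 30 / 3 per month = 10 months, within the stated 10–12.

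**1. Improvement rule.** Patients needed: 0.66 × 30 = 19.8, so 20. If a share c starts at the maximum, the largest possible share improved is 1 − c, and the rule is reachable only if 1 − c ≥ 0.66, i.e. c ≤ 34%. In whole patients, with the 20 needed divided by those who can improve:

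| At maximum at baseline | Can improve | Share of these who must improve |
|---|---|---|
| 0 | 30 | 20/30 = 67% |
| 6 | 24 | 20/24 = 83% |
| 9 | 21 | 20/21 = 95% |
| 10 | 20 | 20/20 = 100% |
| 11 | 19 | impossible (best 19/30 = 63.3%) |

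With fewer evaluable patients the pattern is the same. For every n from 24 to 30, any count at the maximum above one third makes the rule unreachable (n = 24: 16 needed; 9 at the maximum leaves 15/24 = 62.5%).

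**2. How likely is it?** The article gives no baseline scores, so these are assumed ranges. If the true share at the maximum is 20%, 30%, 40% or 50%, the binomial chance of 11 or more among 30 is 0.03, 0.27, 0.71 or 0.95. The rule also weakens before it becomes impossible. Assume the aid improves 85% of patients with room to improve, so that each patient improves with probability 0.85 × (1 − c). The chance of reaching 20/30 is then 93% at c = 10%, 65% at c = 20% and 27% at c = 30%.

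**3. SURE 4/4 route.** 20/30 = 66.7% > 66%, so 20 patients pass.

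| 4/4 before | 4/4 after | Net change | Result |
|---|---|---|---|
| 20/30 | 20/30 | 0 | passes |
| 24/30 | 20/30 | −4 (−13 points) | passes |
| 30/30 | 20/30 | −10 (−33 points) | passes |

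In the second row at least four patients have lost a 4/4 score. If the true 4/4 share is 60%, 70% or 80% and the aid does nothing, the rule passes with probability 0.29, 0.73 or 0.97.

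**4. Check on the remedy.** I simulated a four-item score with no effect (patient random effect SD 1.2–2.0 and mean 0 to 1.5 on the logit scale). In all patients, 25–33% improve and an equal share worsen. Among those below the maximum at baseline, 36–50% improve and 20–28% worsen, which is regression to the mean. An improved-versus-worsened comparison confined to that subgroup would therefore favour a useless aid, so it has to be made in all patients.

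**The case against.** The counting is not in dispute; likelihood and consequence are. The knowledge failure needs more than 34% of patients to score full marks before reading the aid, on a test the steering group has yet to write and whose difficulty is still open. The Background says that patients facing several reasonable options often have decisional conflict, which argues against a baseline 4/4 share as high as 80%. This stands: the ceiling and the high baseline are possibilities, not findings.

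A reader might infer that SURE success becomes unreachable under a ceiling. It does not, because the 4/4 route stays open to patients who start at the maximum; only knowledge lacks a second route. A reader might also infer that a useless or harmful aid would pass the field test. The article does not support that: SURE is part of one of five criteria, and knowledge improvement, a PDMS score of at least 66, acceptability and balance, the 80% feasibility targets and the absence of insurmountable barriers must also be satisfied. Nor do the improvement rules pass easily by chance, since 25–33% improving with no effect is far below 66%.

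Finally, there is no automatic stop or go. A miss leads to steering-group discussion, revision and optional further testing. Strengths and limitations already calls the endpoints arbitrary, and the planned pre/post test could show a net fall. That admission, however, mentions neither the ceiling nor the missing baseline link, and the pre/post test is not among the success criteria.

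**Conclusion.** The point holds as a conditional one. As written, the improvement rule cannot be met at n = 30 once 11 or more patients (36.7%) start at the maximum, and it becomes demanding well before that; for knowledge nothing offsets this. The SURE 4/4 rule can be met with no change if the baseline 4/4 share already exceeds 66%, and with a net fall if it is higher still. No criterion counts patients who worsen.

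The probabilities rest on assumed baseline shares, independent patients and, for the 93%, 65% and 27% figures, an assumed 85% improvement among those able to improve. The counts rest only on n and the stated cutoffs. These are secondary success criteria in a feasibility study and they inform a discretionary revision decision, so this should be fixed but does not threaten the primary outcome.

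**What to change.** Reword Table 1 and the success criteria in Data management and analysis before results are seen:

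1. Apply the 66% improvement rule, for knowledge and SURE, to patients below the maximum at baseline. With 10 of 30 at the maximum this asks for 14 of 20 (0.66 × 20 = 13.2) instead of 20 of 20; with 11 it asks for 13 of 19 (0.66 × 19 = 12.54).
2. Present the full pre/post transition table for all patients, including those who start at the maximum. Require that, among all patients with paired data, the number worsened does not exceed the number improved.
3. Keep more than 66% at SURE 4/4 as a success route only if the paired share at 4/4 is not lower after than before. A condition of not lower is preferable to strictly higher, which a group starting at 30/30 could never meet.

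The cost is wording only, with no new data or patients. The downsides are a smaller denominator for the improvement percentage and some regression to the mean in that subgroup, which is why worsening is counted in all patients.
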